| **Methods:** | Design:  Aim 1 will consist of one-arm pilot of a lead Lead Risk Survey and risk reduction messaging. We will leverage a recent young child cohort in Nairobi (ABC; P22/01/202; N=350; anticipated child age 36 to 48 months), to examine in-clinic survey accuracy and the understandability and acceptability of risk reduction messaging using concurrent home observation and cognitive interviews in a subset with high child blood lead level (BLL). We will use exit in-depth interviews (IDIs) to further refine the survey and risk reduction messaging.  Aim 2 will consist of a randomized trial. Parent-child dyads (child age 12 to 72 months) attending routine well-child visits will receive lead point-of-care testing and complete the Lead Risk Survey (up to N=1,500). Those with high BLL (N=100) will be randomized to 1) immediate in-clinic messaging tailored per their survey (n=50) or 2) immediate in-clinic messaging and addition of home observation and reinforced messages tailored per home findings (n=50).  Aim 3 will consist of a qualitative study. Exit in-depth interviews (IDIs) administered to parents of children with high BLL will be used to identify individual level barriers to uptake of risk reduction measures. Key informant interviews (KIIs) with key informants will be used to identify broader structural barriers to inform policy. |
| **Population:** | Parent-child dyads in Nairobi, Kenya |
| **Sites:** | Dandora II Health Centre, Baba Ndogo Health Centre, Kariokor Health Centre, Kariobangi Health Centre, and Eastlands Health Centre |
| **Study Duration:** | May 1, 2025 – April 30, 2030 |
|  |  |
| **Subject Participation Duration:** | Aim 1: 6 months, Aim 2: 9 months, Aim 3: qualitative data collection only |
| **Estimated Time to Complete Enrollment:** | Aim 1: 1 year, Aims 2 and 3: 1 year |
| **Outcomes:** | Aim 1: Acceptability, understandability of lead exposure program protocol, survey self-report vs. at home observation, refined survey instrument and messages.  Aim 2: Recall of messaging, behavior change to reduce exposure, uptake of blood lead level re checks, and child blood lead level change.  Aim 3: Barriers to behavior change, understandability, acceptability and appropriateness of the lead testing program. |

INTRODUCTION

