**Question 1. How can we develop a Lead Risk Survey developed for parents to be understandable, acceptable, and accurate?**

Hypotheses: This is not a hypothesis driven question. We will use parent response to modify/hone the survey for understandability and acceptability. We will compare home observation to clinic based risk reporting to improve the survey.

**Question 2. Do parent participants in an intervention program (LEIP) have good recall of lead exposure source and action steps at 6 and 9 months and does it vary based on how they received messages and the initial severity of the child’s BLL? (primary outcomes) Do participant children return for BLL recheck and is there a change in their BLL at recheck at 9 months? (exploratory outcomes)**

Hypotheses: Recall of risk factors and uptake of messaging will be high in both parents receiving messages in-clinic only and at-home. Messaging uptake will be highest for dyads with higher BLL. More than half of participants will attend follow up blood level rechecks. On average, blood lead levels will decline over the follow up period.

**Question 3. What are the barriers to uptake of lead risk reduction messaging from the perspective of parents participating in LEIP (Aim 2) and key stakeholders?**

Hypotheses. Barriers to risk reduction will include lower household socioeconomic status, lower self-efficacy, and parent occupation in industries involving e-waste, and proximity of housing to lead-contaminated soil.

GENERAL OBJECTIVE

We seek to develop and implement a novel lead testing program in Nairobi.

Specific Aims

Aim 1. Adapt, pilot and refine a prototype child lead exposure risk survey and messaging protocol

Aim 2. Evaluate uptake of tailored risk reduction messaging delivered in clinic vs at home

Aim 3. Evaluate barriers at individual and structural levels

METHODS

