### *Aim 1 Follow-up Procedures:*

Follow-up procedures will only involve children with high BLL. Briefly, participating parents of these children will be offered a home visit that includes environmental sampling (described below).

1. Home visit. Home visits will be conducted within 2-4 weeks of the lead POC test, or according to the parent’s preference or the study team’s capacity. During the home visit, procedures will include:
2. The Lead Risk Survey will be re-administered and a Home Observational Checklist will be used to identify and discuss residential features and items in child’s home environment that may be influencing the high BLL.
3. Tailored messages on lead exposure risk reduction will be provided.

As possible, items and media that are suspected contributors (e.g., soil near the home where the child plays/spends time, house dust, cooking pots and utensils, cosmetics, spices, toys, painted walls and surfaces) will be tested for lead in situ using an XRF device and documented with photos. These devices can measure lead safely in a variety of household exposure media including dust and soil, painted walls, cookware, children’s toys and clothing, and cosmetics. GPS coordinates will be obtained.

d. Environmental media samples (e.g., soil, the child’s main water source) will be collected for analysis.

1. Home Visit In-depth Interview (IDI). Home visit participants will be asked to participate in IDIs on understandability and acceptability of risk reduction messages and participant anticipated facilitators and barriers to uptake of recommended exposure reduction measures. This will be conducted on the same day or an alternate time based on participant preference. Interviews will be conducted as described above under *“Lead Risk Survey IDI.”*
2. BLL re-check visits. Participants with high BLL will be offered a return to clinic for BLL re-checks at 6 months post lead POC test (a natural timepoint for ABC participants). The re-check will be administered using the POC testing protocol described above. A venous blood sample will be collected.
   1. Referrals as described above will be made for any child who is found to have a newly identified BLL > 25 ug/dL.
   2. Parents will respond to standardized questionnaires to assess their knowledge of exposure risk factors discussed at the time of BLL testing and the home visit and uptake of recommended reduction measures.

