## **Study Records Retention**

After data collection and initial data analysis are complete, we will retain the link between study code numbers and direct identifiers for the length of time required by US state and/or federal law, and Kenyan law, to maintain integrity of study data. After this period, the links to identifiable data for this cohort will be destroyed.

ANALYSIS PLAN

**Aim 1 primary outcomes will be survey understandability and acceptability, agreement between in-clinic and at-home administered survey items and understandability and acceptability of risk reduction messages**. Qualitative analysis of understandability and acceptability. Transcripts of the interviews will be fed into the Dedoose data management tool for analysis. We will conduct a rapid analysis to summarize themes on understandability and acceptability of survey items and messages. The rapid analysis will also explore facilitators and barriers to uptake of recommended exposure reduction measures, and individual level determinants associated with uptake (e.g., empowerment, self-efficacy). Using exit interview transcripts, we will use a hybrid inductive and deductive thematic analysis approach based on our *a priori* selected CFIR constructs. Two coders will independently code transcripts, and generate a comprehensive codebook based on the CFIR constructs and conduct a thematic analysis. If new constructs emerge during our predominantly deductive coding, we will include them inductively. Agreement between in-clinic and at home surveys. Weekly field and co-investigator team meeting discussions will review any observed non-agreement between data from in-clinic and at-home surveys for refinement of this survey in Aim 2.

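### The Aim 1 accuracy question is clinic self-report against home observation, but the Analysis Plan, read literally, compares two self-reports by the same parent

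*Protocol*

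**What the plan says.** Two parts of the protocol set the comparison as self-report against observation. The Structured Summary gives the Aim 1 purpose as "to examine in-clinic survey accuracy and the understandability and acceptability of risk reduction messaging using concurrent home observation" and lists among the outcomes "survey self-report vs. at home observation". Study Questions and Hypotheses asks "How can we develop a Lead Risk Survey developed for parents to be understandable, acceptable, and accurate" and answers: "We will compare home observation to clinic based risk reporting to improve the survey".

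The Analysis Plan names a different pair. Among the Aim 1 primary outcomes it lists "agreement between in-clinic and at-home administered survey items". The only analysis given for it is that weekly meetings will "review any observed non-agreement between data from in-clinic and at-home surveys for refinement of this survey in Aim 2".

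The Aim 1 Follow-up Procedures show that the home visit uses two instruments: "The Lead Risk Survey will be re-administered and a Home Observational Checklist will be used". Table 4 describes the Lead Risk Survey as self-report of risk factors. It lists the observed home findings in a separate row: chipping paint, glazed pottery, aluminium pots and kohl.

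**The concern.** If the at-home survey is the repeated Lead Risk Survey, both sides of the agreement outcome come from the same parent answering the same questions. That tells us whether answers are stable, not whether they are right. A parent who does not know that the paint is chipping, or that a pot or cosmetic is suspect, can give the same wrong answer twice, and the weekly review would have nothing to discuss.

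Aim 1 is the step at which the survey is checked before the Aim 2 trial. In Aim 2 the in-clinic messages are tailored to survey answers, and the clinic-only arm has no home visit to catch a missed hazard. A survey item that is repeatable but inaccurate could therefore lead to less complete messaging.

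The comparator is a separate matter from the interval of about 2 to 4 weeks, and the messaging, between the two surveys. The same point would apply if both were done on one day.

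**Working it through.** **Passages side by side.**

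| Place in the protocol | First measurement | Second measurement |
| --- | --- | --- |
| Structured Summary, Outcomes | Survey self-report | Home observation |
| Question 1 | Clinic-based report | Home observation |
| Analysis Plan, primary outcome | In-clinic survey items | At-home survey items |
| Analysis Plan, weekly review | In-clinic survey | At-home survey |
| Analysis Plan, secondary | Proportion of mothers with actionable targets by self-report | Proportion of assessed homes with actionable targets |

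The last row does use observed findings, but it sets one proportion beside another and describes the number and types of targets per participant. It does not match each answer to each finding. Two proportions can be equal while missed and over-reported items offset each other.

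**Size of the gap.** The protocol states no agreement value, sample size or power for this outcome, so there is no figure to reproduce. What follows is an illustration with assumed inputs: one yes/no item, 20 homes, hazard present in 10, 4 of those 10 parents answering no, no false positives, and observation taken as the truth.

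*Clinic answer against observation:* 6 true positives, 4 missed, 0 over-reported, 10 true negatives.
- Observed agreement = (6 + 10)/20 = 0.80.
- Chance agreement = (6/20)(10/20) + (14/20)(10/20) = 0.15 + 0.35 = 0.50.
- Kappa = (0.80 − 0.50)/(1 − 0.50) = 0.60.
- Sensitivity = 6/10 = 60%.

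*Clinic answer against repeat answer:* if all 4 misreports are repeated, agreement is 20/20 and kappa 1.00. None of the 4 is flagged.

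*Partial repetition:* if 2 of the 4 parents change their answer at home, agreement between surveys is 18/20 = 90%. Two misreports are flagged and two are not. If none is repeated, all 4 are flagged. The number left unflagged is 4 times the share repeated.

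**Range.** Let p be the prevalence of the hazard and s the sensitivity of self-report, with specificity 100%. Agreement with observation is 1 − p(1 − s). The reported-positive share is q = ps, chance agreement is qp + (1 − q)(1 − p), and kappa follows as above.
- p = 0.75, s = 0.40: agreement = 1 − 0.45 = 0.55. Chance = 0.30 × 0.75 + 0.70 × 0.25 = 0.40. Kappa = 0.15/0.60 = 0.25.
- p = 0.25, s = 0.80: agreement = 1 − 0.05 = 0.95. Chance = 0.20 × 0.25 + 0.80 × 0.75 = 0.65. Kappa = 0.30/0.35 = 0.86.

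Over p from 25% to 75% and s from 40% to 80%, agreement with observation runs from 55% to 95% and kappa from 0.25 to 0.86. Fully repeated misreporting gives 100% and 1.00 between surveys throughout.

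**The case against.** The strongest reply is that this is loose wording rather than a chosen comparator. The Structured Summary and Question 1 commit to home observation, and nothing withdraws that. The follow-up procedures name the repeat survey and the checklist in one step, and the Aim 2 enrollment section once calls the checklist a survey. The authors may mean the whole home assessment. This is fair, and a reader should not infer that observation has been abandoned. But the follow-up procedures still treat the two as separate instruments, and the literal sense of the primary outcome is the repeated questionnaire. If the wider meaning is intended, the Analysis Plan has to say so.

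A reader might also infer that observed hazards play no part in revising the survey. The text does not support this: the secondary description of actionable targets is said to feed the adapted Aim 2 survey and messages. That route exists, though it is not an item-level check.

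Nor should the kappa contrast be read as a result the trial would report. The Analysis Plan defines no agreement score, only a review of non-agreement. Full repetition of every misreport is the extreme case, since staff discuss items with the parent at the home visit.

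A bias in Aim 2 recall is not shown either. Recall concerns factors the survey identified, and a missed hazard is not on that list.

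Finally, Question 1 tests no hypothesis and the pilot is formative. That limits the weight of the point but does not remove the inconsistency.

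**Conclusion.** The protocol states the Aim 1 comparison in two ways that do not match. Followed as written, the Analysis Plan checks the repeatability of self-report, whereas the stated question is accuracy, and a misreport repeated at home would go unflagged. The finding rests on the natural reading of the at-home survey as the re-administered Lead Risk Survey. Its size cannot be taken from the documents. The illustrative figures depend on assumed prevalence and sensitivity, perfect specificity, observation taken as truth and, for the extreme contrast, full repetition of misreports.

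The scope is limited. It concerns only items that can be observed; occupation, for example, cannot be checked this way. The comparison would be descriptive, in the roughly 20 high-BLL homes anticipated to accept a visit. It is nonetheless worth settling before Aim 1 home visits are analysed, because it restores the trial's own question at almost no cost.

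**What to change.** In the Analysis Plan, Aim 1 primary outcomes:

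1. For observable items (for example chipping paint, cookware, cosmetics), define the agreement outcome as the in-clinic Lead Risk Survey answer against the Home Observational Checklist finding. For each item, report how many were missed and how many over-reported.
2. Have the weekly meetings review that discordance when revising survey items.
3. Keep clinic-against-home survey agreement as a repeatability measure, and as the available check for items that cannot be observed.
4. Use XRF results only as supporting description where taken. Testing is done as feasible on suspected items, and a lead concentration is not a direct reference for most survey answers.
5. Bring the wording of the Structured Summary, Question 1 and the Analysis Plan into line.

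The cost is protocol wording and a little more descriptive analysis. The checklist and both surveys are already planned at the Aim 1 home visits, so no new data are needed.

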## **Aim 2 Sample Size and Power**

*Sample size:* 1,500 children will be enrolled and undergo POC BLL testing. We anticipate this sample size is required to achieve N = 100 with high BLL (e.g., ≥ 5 ug/dL), based on estimated of high BLL in ABC child participants at age 12 months (8.2%). Should we achieve our target of N = 100 randomized prior to enrolling 1,500 parent-child pairs, we will stop enrollment early.

Parents of these children with high BLL will be randomized to immediate messaging tailored per in-clinic survey alone vs the same protocol along with a home visit for home observational checklist + reinforced messaging per home findings (N = 50 in each arm). Follow up visits at 3 and 9 months will include surveys of message recall, behavior change to reduce exposure, and a BLL recheck.

*Power:* Primary outcomes will be recall of survey identified exposure risk factors and self-reported uptake of risk reduction behavior. Assuming 5% attrition and 10% attrition at the 3 and 9 month re-check visits, respectively, we anticipate n = 95 and n = 90 at re-check visits, respectively. Assuming n = 90, alpha = 0.05, a one-sided test, and an observed recall or uptake of ≥ 67% within an arm, we will have ≥ 80% power to exclude a recall or uptake of < 50%. For an observed recall or uptake of > 43% within an arm, we will have ≥ 80% power to exclude the possibility that recall / uptake is actually < 25%.

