**Secondarily,** we will estimate the proportion of mothers (self-report on in-clinic surveys) and assessed homes with identified actionable targets, e.g., suspect household products, including cosmetics, chipped paint, potential occupational exposure, or other lead containing items observed using direct read instrumentation). We will describe the number and types of actionable targets identified for each participant. These data will enhance our adapted survey and messaging protocols for Aim 2. We will summarize descriptive statistics for standardized questionnaires on recall of identified risk factors, behavior change (e.g., proportions with recall of all or some factors vs. proportions with recall of some or no factors) and Risk, Ability and Attitude (e.g,, proportions with strong agreement vs. weak or no agreement). We will select questions with higher variability, and we will refine our questionnaires as appropriate for use in Aim 2.

**Aim 2 primary outcomes will be recall of risk reduction messages, and self-report risk reduction behavior. Exploratory outcomes will be uptake of the BLL re-check and change in BLL.** Balance between arms. We will compare baseline characteristics between randomization arms to evaluate balance of demographic and risk survey characteristics. We will use chi-square tests for dichotomous variables and rank sum tests or t-tests, as appropriate, for continuous variables.

**Recall of risk reduction messages and change in risk reduction behavior.** We will describe the proportion of parents with recall of all or most of their exposure factors identified on their surveys, within each arm and by child BLL. Similarly, we will describe proportions of parents self-reporting uptake of at least one of their risk reduction recommendations within arms and by BLL. We hypothesize that recall and behavior change will be moderate (e.g., greater than 50% in both arms), and that recall and behavior change will be highest for parents in the high BLL strata. Secondarily, we will explore potential differences in outcomes between arms, acknowledging that we will have limited ability to exclude small differences. Finally, we will describe the types of messaging recommendations taken up and not taken up by participants.

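### Aim 2 judges baseline balance by significance tests, which do not measure the size of a chance imbalance, and leaves baseline BLL off the list; only the exploratory between-arm comparison is affected (minor)

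*Protocol*

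**What the plan says.** In the protocol's Analysis Plan, the Aim 2 paragraph on balance between arms states: "We will compare baseline characteristics between randomization arms to evaluate balance of demographic and risk survey characteristics". The next sentence fixes the method: "We will use chi-square tests for dichotomous variables and rank sum tests or t-tests, as appropriate, for continuous variables". No significance level, no size of imbalance that would matter, and no step following from the results is given.

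The primary outcomes, recall and self-reported uptake, are described as proportions within each arm and by child BLL. The comparison of arms comes after that and is qualified: "Secondarily, we will explore potential differences in outcomes between arms, acknowledging that we will have limited ability to exclude small differences".

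Under Study Questions and Hypotheses, Question 2, the protocol predicts that BLL is prognostic: "Messaging uptake will be highest for dyads with higher BLL". The Analysis Plan repeats the prediction for recall and behaviour change. The size of the trial is given under Aim 2 Sample Size and Power: "N = 50 in each arm".

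**The concern.** The task set is to evaluate balance, which is a question about the size of the differences that this randomisation happened to produce. A significance test answers a different question: whether the difference is larger than random allocation would usually give. Allocation is random by design, so that answer is already known. With 50 per arm, a non-significant result is compatible with a moderate difference in a variable that matters.

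The list of variables adds to this. Demographic and risk survey characteristics are named. Table 4 classes blood lead results separately, under point-of-care and laboratory tests. Read as written, the check omits the one baseline value that the protocol itself expects to go with recall and uptake.

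What is at stake is the reading of the arm contrast. The justification for randomisation, under Potential Risks and Benefits, rests on evaluating the two delivery models in similar groups so as to inform policymakers. The planned tests are weak evidence of similarity, and a chance imbalance in BLL could add to or hide a difference of a few points.

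**Working it through.** **Plan's own figure.** There is none to reproduce: the protocol gives no alpha, power or threshold for the balance tests. Its power statement concerns within-arm proportions and does not bear on this point.

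**Inputs.** From the protocol: 50 per arm at baseline. Attrition of 5% and 10% affects follow-up, not the baseline table. Assumed: two-sided 0.05.

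**1. Largest realised difference that passes, continuous variable.** The t-test is significant when d × sqrt(n/2) exceeds t(0.975, 98), where d is the observed difference in pooled SD units.
- Limit: d = 1.984 × sqrt(2/50) = 1.984 × 0.2 = 0.397 SD.
- Anything below about 0.40 SD is non-significant. By contrast, a realised 0.5 SD gives t = 0.5/0.2 = 2.50, p = 0.014, and is flagged.

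**2. How often moderate imbalances arise and pass.** In 200,000 simulated randomisations at 50 per arm, a realised difference of at least 0.25 SD on one covariate occurred 21% of the time, and 77% of those were non-significant. A difference of at least 0.5 SD occurred 1.4% of the time, and the t-test flagged all of them.

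**3. Binary variable, chi-square without continuity correction.**

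| Arms | Gap | p |
|---|---|---|
| 21/50 vs 29/50 | 16 points | 0.11 |
| 20/50 vs 29/50 | 18 points | 0.072 |
| 20/50 vs 30/50 | 20 points | 0.046 |

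With the continuity correction the 20-point gap also passes (p = 0.072).

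**4. Consequence for the arm comparison (illustration).** Assumptions, none from the protocol: half the children in a higher-BLL stratum, uptake 80% there and 50% in the lower stratum, no arm effect, allocation not stratified by BLL, all 50 per arm analysed.
- A stratum imbalance of g points shifts the expected arm difference by g × (0.80 − 0.50).
- The probability that the strata differ by 10 points or more and still have p > 0.05 (uncorrected chi-square) is 25% if exactly 50 of the 100 children are in the higher stratum, and 31% if stratum membership is random in each arm.
- The mean shift in those trials is 3.9 to 4.0 points in the direction of the imbalance. Simulation gave 4.1.
- Overall uptake is (0.80 + 0.50)/2 = 0.65. The standard error of the arm difference is sqrt(2 × 0.65 × 0.35/50) = 0.095, or 9.5 points. The shift is therefore about 4/9.5 = 0.4 of a standard error.
- With stratum adjustment the mean shift was 0.000 in simulation.
- Variance ratio, adjusted to unadjusted: within-stratum variance (0.80 × 0.20 + 0.50 × 0.50)/2 = 0.205, against 0.65 × 0.35 = 0.2275, gives 0.90. Simulation gave 0.91, a reduction of about 9%.

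**The case against.** **The primary results do not rest on balance.** This stands. Recall and uptake are estimated within each arm, and the comparison of arms is secondary, exploratory and already acknowledged as imprecise.

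**No decision hangs on the tests.** This also stands. A reader might infer that a non-significant table will be taken as proof of comparable arms, or that a significant one will trigger adjustment. The protocol says neither.

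**The tests look underpowered.** A reader might apply the usual power of a two-sample test to a half-SD difference and conclude that such an imbalance would often be missed. That does not follow. The calculation concerns a difference between populations, and randomisation leaves none. A realised half-SD imbalance at 50 per arm has p = 0.014 and is flagged. The right limit is about 0.40 SD realised.

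**BLL is not ignored.** Correct in part: outcomes are to be described by child BLL within arms, and a count of risk factors could fall under risk survey characteristics. But describing outcomes by BLL does not show how the arms differ on BLL, and it is not an adjusted comparison.

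**The bias is conditional and small.** Over all randomisations the unadjusted difference is unbiased, and chance imbalance is already part of its standard error. This stands, and limits the weight of the point.

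**Adjustment may sit in a statistical analysis plan not shown.** For that reason its absence is not the finding. The finding is the method and the variable list that the protocol does state.

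**Conclusion.** The point holds in a limited form. The protocol commits to significance tests as the means of evaluating balance between randomised arms, and these do not measure what is wanted. At 50 per arm and an assumed two-sided 0.05, realised differences up to about 0.40 SD, or about 18 points on a binary factor, would be non-significant. The listed variables omit baseline BLL although the protocol predicts that it is prognostic.

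The effect on results is modest: a conditional shift of about 4 points in the exploratory arm difference, under assumed uptake rates of 80% and 50% and equal strata. A weaker relation between BLL and uptake would make it smaller. No primary outcome and no design decision changes. Severity is minor; the reason to act is that the improvement costs almost nothing.

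**What to change.** In the Aim 2 section of the Analysis Plan:

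1. Replace the balance tests with a descriptive baseline table by arm, giving standardised differences and no p-values. Add baseline BLL and the number of risk factors identified on the enrollment Lead Risk Survey.
2. State that the exploratory between-arm comparisons of recall and uptake are adjusted for baseline BLL and that number, whatever the table shows. The modified Poisson regression with robust errors already named under the analysis of implementation strategy mechanisms will serve.
3. Name which baseline BLL measurement is used, since both a point-of-care and a venous value are planned.

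The cost is a change of wording and one further model. The point-of-care BLL and the Lead Risk Survey are collected at enrollment, before randomisation, so no new data are needed. What is lost is the column of p-values in the baseline table.
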